### Observational control cohort

Between 1995 and 1997, the Emilia-Romagna Region started a double-reading mammography screening programme for women aged 50–69 years, which switched from analog to digital mammography (DM) in 2010–2011. The programme was extended to women aged 45–49 years and 70–74 years in 2010, with an annual screening interval for the younger age group [46]. In the context of the RIBBS study, the observational control cohort includes women 45 years of age residing in three provinces of the Emilia-Romagna Region. These individuals participated in the annual screening programme from 2012 to 2020.

The five subgroups of the interventional cohort and the observational control cohort are depicted in Fig. 1.

**Fig. 1 Fig1:**
[figure not shown]
Technical scheme depicting the five subgroups of the interventional cohort and the observational control cohort of the Risk-Based Breast Screening (RIBBS) study

### Pre-screening and screening periods

The pre-screening phase for the interventional cohort ran from 2017 to 2019, while that of the control population ran from 2005 to 2009. Subsequently, the screening phase started in 2020 for the interventional cohort and 2012 for the control population. The screening phase will end in 2026 for the interventional cohort and 2024 for the observational cohort. These timelines are designed to ensure that all women who entered the screening programme at age 45 are screened until they turn 50.

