Both the interventional and control cohorts are studied using a two-phase design involving a pre-screening period followed by a screening period. The pre-screening phase measures the baseline incidence rate of breast cancer in women aged 45–49 years in both populations. This baseline assessment helps calculate the ratio of the incidence rate at baseline between the Veneto Region and the Emilia-Romagna Region for subsequent statistical adjustment. During the screening period, the two screening models are implemented, and cumulative incidence rates of advanced breast cancer are assessed over 3 years, 5 years and 10 years (at least). The ratio of the cumulative incidence rate in the interventional cohort to that found in the observational control cohort, adjusted for differences in incidence at baseline, is calculated. The decision to evaluate the results at three-year intervals stems from previous research that demonstrated a significant decline in the incidence of pT2-4 stage breast cancer from the third year of screening [44]. The extended follow-up duration takes into account the potential lasting preventive impact of screening beyond age 50 and incorporates the common biennial digital mammography screening procedure for women over age 50.

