### Statistical analysis

Regarding the primary objective of the study, which focuses on evaluating the impact of the personalized screening model on the cumulative incidence of advanced breast cancer (stage II or higher), a series of analyses are planned. Person-years at risk and follow-up duration will be calculated for both cohorts, starting from the date of first screening and continuing until the date of censoring or the end of follow-up, whichever comes first. The follow-up duration will be truncated at the 75th percentile of available follow-up times, as determined by the criterion proposed by Puliti et al. [51].

Woman age will be calculated at the date of the first screening. Cumulative age-standardized advanced breast cancer incidence rates will be calculated for both cohorts and then compared using the incidence rate ratio (IRR) along with 95% confidence interval (95% CI). Estimation of IRRs will be obtained by multivariable Poisson regression analysis.

To address potential dissimilarities (if any) in the risk of breast cancer between the two cohorts, incidence rates from the pre-intervention period will be used. Adjusting the IRR of advanced breast cancer will involve multiplying the unadjusted IRRs by the observed/expected ratio within the observational control cohort. Calculation of 95% CIs will be performed by a bootstrap procedure.

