### Study status

In the Veneto Region, enrollment in the interventional cohort began in January 2020 and ended in December 2021, successfully enrolling a total of 10,269 women aged 45 years. Currently, these participants are regularly invited to participate in subsequent screening rounds according to the established schedule. The screening phase for this cohort will extend until December 2026, providing full coverage until women reach age 50. Thereafter, they will enter the target population of the standard two-year mammography screening programme, with routine invitations until age 69.

The observational control cohort comprises women aged 45 years who were enrolled in the annual mammography screening programme between 2012 and 2020 in three provinces of the Emilia-Romagna Region, for a total number of 43,840 women. As in the Veneto Region, when these women cross the 50-year threshold, they will become part of the population eligible for biennial mammography screening.

Follow-up evaluations will continue for at least 10 years after the enrolment in the study.

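### The two baseline periods lie 11 years apart but the screening periods only about 4.5, so the baseline adjustment leaves roughly 6 to 6.5 years of any shared trend in the primary IRR

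*Protocol article*

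**What the plan says.** The section on pre-screening and screening periods fixes the baselines: "The pre-screening phase for the interventional cohort ran from 2017 to 2019, while that of the control population ran from 2005 to 2009". It adds that "the screening phase started in 2020 for the interventional cohort and 2012 for the control population", and that "The screening phase will end in 2026 for the interventional cohort and 2024 for the observational cohort". Study status gives the entry windows: "enrollment in the interventional cohort began in January 2020 and ended in December 2021", and control women were "enrolled in the annual mammography screening programme between 2012 and 2020 in three provinces of the Emilia-Romagna Region".

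The Study design section says the baseline data serve to "calculate the ratio of the incidence rate at baseline between the Veneto Region and the Emilia-Romagna Region for subsequent statistical adjustment". The Statistical analysis section describes the step differently: "Adjusting the IRR of advanced breast cancer will involve multiplying the unadjusted IRRs by the observed/expected ratio within the observational control cohort". It does not say how the expected number is obtained.

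Study limitations names this adjustment as the answer to bias from non-randomisation. It also says that missing data on the reference population rule out formal adjustment for confounders. Nowhere does the article project baseline rates forward, name a calendar-time term, or mention that the two regions have different lags between baseline and screening.

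**The concern.** A pre-post comparison with a non-equivalent control removes a shared calendar trend only if the time from baseline to outcome is the same in both groups. Here it is about 5 years in Veneto and about 11.5 in Emilia-Romagna. The baseline ratio is meant to measure a regional difference in risk, but it also contains 11 years of calendar change, and the screening-period comparison contains only about 4.5 years of it.

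The excess goes into the primary estimate through the step that is meant to protect it. More women would not reduce it. Nor would longer follow-up of equal length in both cohorts, because both person-time midpoints then move together.

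**Working it through.** **The plan's own figure first.** Sample size gives 43,000 and 10,269 women, 5 years, a control rate of 0.004017, one-sided alpha 0.05, and 80.5% power at a rate ratio of 0.810.

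- Expected control events: 43,000 × 5 × 0.004017 = 863.7.
- Expected interventional events: 10,269 × 5 × 0.004017 × 0.81 = 167.1.
- SE of the log ratio: √(1/863.7 + 1/167.1) = 0.0845. Then |ln 0.81|/0.0845 - 1.645 = 0.848, which gives 80.2% power.
- A variance-stabilised square-root statistic with the 3/8 correction gives 82.0%.

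The stated power is reproduced closely and is not in dispute. It takes no account of the bias below.

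**Calendar midpoints** (whole calendar years; uniform entry is assumed because no yearly counts are given).

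| | Veneto | Emilia-Romagna | Gap |
|---|---|---|---|
| Baseline | 2018.5 | 2007.5 | 11.0 |
| Entry | 2021.0 | 2016.5 | 4.5 |
| 5-year person-time (entry + 2.5) | 2023.5 | 2019.0 | 4.5 |
| Lag, baseline to person-time | 5.0 | 11.5 | |

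Uncancelled years = screening gap - baseline gap = 4.5 - 11.0 = -6.5. Cutting person-time at the stated ends of the screening phases gives -6.4. Using phase midpoints (2023.5 and 2018.5) gives 5.0 - 11.0 = -6.0. The result therefore does not hinge on the entry assumption.

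**Bias factor.** Take the adjusted IRR as the screening-period ratio divided by the Veneto/Emilia-Romagna baseline ratio, with one log-linear trend g shared by both regions and by baseline and outcome. The factor is (1+g)^4.5 / (1+g)^11 = (1+g)^-6.5. The values of g are assumptions. The error rates use the plan's event counts and ignore sampling error in the baseline ratio.

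| g per year | Factor, exponent -6.5 | Factor, exponent -6.0 | True 0.81 appears as | One-sided type I error | Power at 0.81 |
|---|---|---|---|---|---|
| -2% | 1.14 | 1.13 | 0.92 | <0.1% | 24% |
| -1% | 1.07 | 1.06 | 0.87 | 0.6% | 53% |
| 0 | 1.00 | 1.00 | 0.81 | 5% | 80% |
| +0.5% | 0.97 | 0.97 | 0.78 | 11% | 89% |
| +1% | 0.94 | 0.94 | 0.76 | 21% | 95% |
| +2% | 0.88 | 0.89 | 0.71 | 51% | 99% |

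**Dependence on the baseline endpoint.** Study design describes the baseline as breast cancer incidence, whereas the primary outcome is stage II or higher. If the baseline is all breast cancer, the factor becomes (1+g_adv)^4.5 × (1+g_all)^-11. With assumed g_all = 1% and g_adv = 0 it is 0.90. With g_all = 1% and g_adv = 2.5% it is 1.00, so two rising trends can offset each other.

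**Dependence on the formula.** If the expected count means Veneto baseline rates applied to the control population at baseline, multiplying by observed/expected is the same as dividing by the baseline ratio, and the table applies. If it instead means control cases in the screening period as expected from 2005-2009 rates, the control screening-period rate drops out. What remains is the Veneto screening-period rate over the Emilia-Romagna 2005-2009 rate. That carries 2023.5 - 2007.5 = 16 years of trend in the opposite direction: 1.17 at g = +1% and 1.37 at +2%.

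**The case against.** The windows have a visible reason. The control-cohort section says Emilia-Romagna extended screening to ages 45-49 in 2010, so 2005-2009 is its last period before that change; 2017-2019 is the last such period in Veneto. The article openly concedes weaker internal validity and possible contextual effects, and an unseen analysis plan could hold a trend sensitivity analysis. All of this is fair, but it explains the mismatch without removing it. The windows and the multiplicative step are fixed in this article. A calendar term in the Poisson model would not by itself align a factor that is multiplied on afterwards.

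Some stronger readings are tempting, and the document does not support them:

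- A reader might infer that better detection over time pushes the adjusted IRR below 1. The outcome is stage II or higher, which earlier detection would tend to lower. Under the Study design ratio a falling trend pushes the adjusted IRR above 1.
- A reader might infer that trend could explain the whole planned effect, since 0.81^(-1/6.5) - 1 is about 3.3% per year. No trend is given in the article, and this figure also needs baseline and outcome to share one trend.
- A reader might take the baseline ratio to be the only control for confounding. Age-standardised rates and a multivariable Poisson model with unlisted covariates are also planned.

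**Conclusion.** The point stands. Under the Study design ratio, about 6 to 6.5 years of any trend common to both regions stays in the primary IRR. Trends of 1% to 2% per year, if present, would move the adjusted IRR by roughly 6% to 14% in either direction. That is enough to alter type I error or power materially against a planned ratio of 0.81.

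This rests on uniform entry, a log-linear trend shared by the regions, and one trend for baseline and outcome. The document does not show that the adjusted IRR will be biased in favour of the intervention, or by any particular amount. Without a trend there is no bias, and size and sign stay open until the baseline endpoint and the expected count are defined. What it does show is that the named safeguard works only if incidence was nearly flat or the trends happen to offset, and the article neither claims nor tests either.

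**What to change.** 1. State one adjustment formula that agrees between Study design and Statistical analysis, define the expected count, and use the baseline rate for the primary endpoint (stage II or higher).
2. Project each region's baseline rate to the calendar years of its own screening person-time. Estimate the trend from the unscreened Veneto 45-49 series up to 2019 and, where available, the 2005-2009 Emilia-Romagna data. Alternatively, fit one Poisson model with region, calendar year and screening period. The planned bootstrap should then carry the uncertainty of the baseline rates and the trend.
3. Report the adjusted IRR over a pre-set trend range such as -2% to +2% per year. Make this the minimum if earlier Veneto registry data are incomplete.

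Using 2005-2009 in both regions without a trend term is not enough. The baseline gap becomes zero but the 4.5-year screening gap remains, giving (1+g)^4.5, or 1.05 at +1% and 1.09 at +2%, now in the other direction.

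The cost is aggregate registry counts for additional Veneto years and a revised analysis, with no change for participants. The downsides are reliance on registry coverage and stage completeness in earlier years (not stated in the article), the assumption that an extrapolated trend applies to both regions, and a wider interval.

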### Study hypothesis

The interventional cohort is stratified into five subgroups based on breast density and individual risk, each associated with an imaging protocol expected to have greater sensitivity than mammography in the control cohort. The two-year screening interval for the two low-risk interventional subgroups (with low and high density, respectively) compared with the control cohort (annual mammography) does not denote de-escalation, as digital breast tomosynthesis remains more sensitive than mammography. In brief, the study hypothesis predicts the superiority of the personalized screening approach in decreasing the cumulative incidence of advanced breast cancer compared with the conventional “one-size-fits-all” mammography screening procedure.

### Outcome measures

The primary and secondary outcome measures are listed in Table 1. The primary measure of the effectiveness of screening stratified by breast density and risk, compared with conventional annual mammography, will be the cumulative incidence of advanced breast cancer. In particular, the focus will be on stage II or higher cancer throughout the follow-up period. Most of the secondary outcome measures are part of the core indicators used in the annual national survey of regional mammography screening programmes in Italy. These indicators were defined by the Italian Group for Mammography Screening and the Italian National Centre for Screening Monitoring [48]. They constitute the benchmark for reporting outcomes of breast cancer screening programmes in Italy.

**Table 1 Tab1:** Primary and secondary outcome measures in the RIBBS study

	Description
Primary outcome meausure: cumulative incidence of advanced breast cancer	Measure of effectiveness of screening stratified by breast density and risk compared with standard annual digital mammography. Focuses on stage II or higher cancer throughout the follow-up period
Secondary outcome measures	
Recall rate	Number of women recalled for further diagnostic evaluation per thousand women undergoing each of the two screening protocols
Cancer detection rate	Number of women with breast cancer detected by screening (topographic code C50 [47]) per thousand women undergoing each of the two screening protocols
Proportional incidence of interval cancer	Number of women diagnosed with interval cancer (detected after a negative screening episode) divided by the expected number of breast cancer cases in the absence of screening, by screening protocol and interval year
Total assessment rate	Number of women undergoing diagnostic evaluation per thousand women undergoing each of the two screening models, further subdivided into non-invasive and invasive assessment rates
Surgical referral rate	Number of women referred for excisional biopsy or definitive surgical treatment per thousand women undergoing each of the two screening protocols
Surgery rate	Number of women undergoing excisional biopsy or definitive surgical treatment per thousand women undergoing each of the two screening protocols
Benign lesion detection rate	Number of women with any histologically diagnosed benign lesion per thousand women undergoing each of the two screening protocols
Tumour-stage specific detection rate	Number of women with cancer detected by screening and classified by TNM tumour stage per thousand women undergoing each of the two screening protocols
Regular re-screening rate	Number of women who regularly undergo the specific screening protocol (within ± 3 months) between ages 45 and 49 per thousand women in the interventional and control groups. Calculated for the total interventional cohort and the observational control cohort

Table 2 provides an overview of the additional analyses planned as part of the RIBBS study.

**Table 2 Tab2:** Additional analyses planned as part of the RIBBS study

Analysis definition	Description
Cost and organizational impact analysis	Examines both the direct costs associated with implementing and operating the stratified screening programme, as well as the economic feasibility and financial implications of adopting the personalized approach. Evaluates expenses related to screening equipment, staff training, data management systems, and potential changes in workflow and resource allocation within screening units. Provides insights for policy makers, healthcare administrators, and stakeholders involved in decision-making regarding breast cancer screening strategies
Impact of breast cancer risk model on personalization of screening	Compares the proportions of women categorized as low, intermediate, and high risk for breast cancer using different risk models (Tyrer-Cuzick, Gail, Boadicea) to assess risk stratification implications in personalized screening
Impact of breast density metrics on personalization of screening	Compares the proportions of women with dense and non-dense breasts using various breast density metrics (Volumetric Breast Density, Area-Based Breast Density, BI-RADS category) to evaluate breast density stratification implications in personalized screening
Impact of different breast density metrics on breast cancer risk assessment	Compares proportions of women classified as low, intermediate, and high risk using the Tyrer-Cuzick risk model when different breast density metrics are utilized. Examines implications of different density measures for risk stratification in personalized screening
Prevalence analysis of breast cancer subtypes	Evaluates the distribution by breast cancer subtype (luminal A, luminal B, HER2-positive, basal-like) across the overall study population and when stratified by breast density and risk category. Analyses subtype prevalence variations according to breast density and individual risk profiles
Potential of artificial intelligence (AI) to supportpersonalization of screening	Explores AI integration into personalized screening protocols. Assesses potential reduction in readers needed for personalized protocols with double reading and workload reduction from AI's accurate classification of clearly negative exams. Evaluates benefits like cost savings, efficiency, resource utilization, radiologist productivity, and job satisfaction. Measures AI effectiveness in different subgroups based on breast density and risk categories

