### Interventional cohort

The prospective interventional cohort consists of women aged 45 years from two provinces in the Veneto Region. The enrollment phase for this cohort has been completed, with a final number of participants of 10,269 women. Participants initially met specific criteria and are now undergoing successive screening rounds with different intervals and imaging protocols until the age of 50.

During the initial screening round, participants underwent two-view digital breast tomosynthesis (DBT) of both breasts. They also completed a questionnaire on risk factors such as personal characteristics, hormonal factors, family history of breast cancer, lifestyle, and health status. Volumetric breast density (VBD) values were calculated with Volpara software from DBT images [45]. Subsequently, women with an average VBD greater than 25% were invited for supplemental ultrasound (US). Based on individual risk factors and mean VBD, we used the Tyrer-Cuzick risk model to estimate lifetime risk (LTR) for each woman [17, 22]. This risk assessment categorized women into five subgroups each recommended for a personalized screening protocol:*Low-Risk, Nondense Breasts*: Women with LTR ≤ 17% and VBD < 25% are recommended for biennial DBT screening;*Low-Risk, Dense Breasts*: Women with LTR ≤ 17% and VBD ≥ 25% are recommended for biennial DBT screening with supplemental US (DBT + US protocol);*Intermediate-Risk, Nondense Breasts*: Women with LTR between 17 and 30%, or LTR > 30% without family history, and VBD < 25% are recommended for annual DBT screening;*Intermediate-Risk, Dense Breasts*: Women with LTR between 17 and 30%, or LTR > 30% without family history, and VBD ≥ 25% are recommended for annual DBT + US screening;*High-Risk, Any Breast Density*: Women with LTR > 30% and a family history of breast cancer, are recommended for annual DBT and magnetic resonance imaging (MRI) surveillance, regardless of breast density.

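### Read as requiring every round, the regular re-screening rate asks for four on-time returns under annual screening but two in the biennial subgroups, so the cohort totals cannot be compared as adherence

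*Protocol article*

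**What the plan says.** All references are to the protocol article.

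- **Numerator** (Outcome measures, Table 1, regular re-screening rate): "Number of women who regularly undergo the specific screening protocol", with a tolerance of 3 months either side. The unit is the woman, and the yardstick is her own protocol.
- **Span and denominator** (same row): "between ages 45 and 49 per thousand women in the interventional and control groups". Nothing divides by the number of rounds due.
- **Level of reporting** (same row): "Calculated for the total interventional cohort and the observational control cohort". The row names only these two totals, so the five interventional subgroups are pooled.
- **Control schedule** (Observational control cohort): the programme was extended to women aged 45-49 "with an annual screening interval for the younger age group".
- **Interventional schedules** (Interventional cohort): low-risk women with nondense breasts "are recommended for biennial DBT screening", and low-risk women with dense breasts have the same interval with ultrasound added. The Study hypothesis section confirms this with "The two-year screening interval for the two low-risk interventional subgroups". Intermediate-risk women with nondense breasts "are recommended for annual DBT screening". The intermediate-risk dense and the high-risk subgroups are also annual.
- **Duration** (Pre-screening and screening periods): the timelines are meant to ensure that "all women who entered the screening programme at age 45 are screened until they turn 50".

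**The concern.** The measure is all-or-nothing per woman, and the number of occasions on which she can fail depends on her screening interval. Annual and biennial women are pooled in one cohort and set beside a cohort that is entirely annual. The two totals therefore mix two things: how reliably women return when a return is due, and how many returns are due.

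This is the only outcome in Table 1 that measures continued participation, and the study sets out to assess feasibility as well as efficacy. A difference between the totals could be taken as a difference in adherence when part or all of it comes from the definition. The measure could also hide poorer adherence per visit in the interventional cohort.

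**Working it through.** The document gives no value for this outcome, so there is no figure to reproduce.

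**Step 1: returns due.** These counts are derived from the stated intervals and ages; the article does not print them. The first screen is at 45.
- Annual: returns at 46, 47, 48 and 49, so four.
- Biennial: returns at 47 and 49, so two.

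**Step 2: formula.** Let p be the probability that a due return is on time, equal in both cohorts, and s the share of the interventional cohort on biennial screening. The document gives neither, so both are assumptions. If every round must be kept, returns are independent and all women share the same p:
- control rate = p⁴
- interventional rate = s·p² + (1 − s)·p⁴
- difference = s·p²·(1 − p²), which is above zero whenever 0 < p < 1 and s > 0.

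**Step 3: numbers with one common p** (per 1000 women).

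| p | Control, p⁴ | Biennial subgroups, p² | Interventional total, s = 0.6 to 0.8 | Difference in points |
|---|---|---|---|---|
| 0.85 | 522 | 722 | 642 to 682 | 12 to 16 |
| 0.90 | 656 | 810 | 748 to 779 | 9 to 12 |

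For p = 0.85: 0.7225 − 0.5220 = 0.2005; × 0.6 = 0.120 and × 0.8 = 0.160.

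**Step 4: women who differ in adherence.** Let p follow a beta distribution across women with mean 0.85 and concentration k, the same for annual and biennial women. With a = 0.85k, the chance of keeping n returns is the product of (a + i)/(k + i) for i = 0 to n − 1.
- k = 1, two returns: 0.85 × 1.85/2 = 0.786. Four returns: 0.786 × 2.85/3 × 3.85/4 = 0.719. Difference 0.067; × 0.6 to 0.8 gives about 4 to 5 points.
- k = 2, two returns: 0.85 × 2.7/3 = 0.765. Four returns: 0.765 × 3.7/4 × 4.7/5 = 0.665. Difference 0.100; × 0.6 to 0.8 gives about 6 to 8 points.

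Strong variation between women shrinks the artefact but does not reverse it. It vanishes only if every woman has p equal to 0 or 1.

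**Step 5: what could be masked.** With one common p and s = 0.7, suppose control returns are on time with p = 0.80, giving 0.80⁴ = 0.410. An interventional cohort with p of about 0.696 gives 0.7 × 0.696² + 0.3 × 0.696⁴ = 0.339 + 0.070 = 0.409. The totals match although adherence per return is about 10 points lower.

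**Step 6: effect of the change.** On-time returns divided by returns due has expectation p under either interval, for example 850 per 1000 in both cohorts at p = 0.85. The artefact is gone.

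**The case against.** **The article does not define what counts as regular.** This is right, and scoring detail may sit in a fuller document. Requiring every round is the natural reading of keeping to one's own schedule across the span, but it is a reading, and the direction of the artefact rests on it. If keeping at least half the rounds sufficed, p = 0.85 would give 1 − 0.15⁴ − 4 × 0.85 × 0.15³ = 0.988 under annual screening and 1 − 0.15² = 0.978 under biennial, a slight tilt the other way. The totals would still not measure adherence on a common scale.

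**Completing one's own schedule is a legitimate target.** This also stands. If a longer interval is easier to complete, that is a real property of the programme. It justifies keeping the rate as a description, but not reading the gap between totals as adherence.

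**The tolerance is tighter, relative to the interval, for biennial women:** 3 of 24 months against 3 of 12. If timing error grows with the interval, this offsets part of the gap. It is another reason the totals are not like for like.

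**Stronger readings that the document does not support.** A reader might infer that the study will present a higher interventional rate as better adherence, or as proof of feasibility. No section says so: the row gives no test, superiority criterion or threshold, and the hypothesis that the stratified model is more sustainable is not tied to this rate. A reader might also take 12-16 points as the size of the bias. That figure is the end of the range with no variation between women. Nor does the whole interventional cohort need only two returns; three of its five subgroups need four, as control does.

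**Conclusion.** The point holds in a conditional form. If regular means every round, and the on-time probability per return is equal, the pooled interventional total exceeds the control total because some of its women have fewer returns to keep. The two totals should not be compared as adherence.

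The size cannot be settled from the document, which gives neither the on-time probability, nor its variation between women, nor the biennial share. At an assumed mean of 85% and a biennial share of 60-80%, it is about 12-16 points with one common independent probability and about 4-8 points under strong variation.

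This is one of nine secondary outcomes. The primary comparison of advanced cancer incidence is untouched, so the point is a low-cost improvement and does not call for dropping the outcome.

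**What to change.** Keep the rate in Table 1 as a description of schedule completion within each cohort, and state whether it requires every round. For the between-cohort comparison, add on-time returns divided by returns due, with standard errors clustered by woman, and report it by screening interval as well as in total. The split matters because an annual woman contributes four due returns to the pooled ratio and a biennial woman two, so the total leans towards the annual subgroups if adherence differs between them.

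The cost is one extra analysis of a secondary outcome. Data collection and management says that the control data warehouse holds invitations and mammograms, and Study status says that interventional women are invited on a set schedule, so no new data collection should be needed. Retaining the existing rate also protects comparability should it be one of the national core indicators, which the article does not make clear.

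The change does not remove other differences between the cohorts. In particular, Table 3 requires willingness to comply with scheduled visits only in the interventional cohort.
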